## Abstract

**Background:**

The Pneumatic CompREssion for Preventing VENous Thromboembolism (PREVENT) trial evaluates the effect of adjunctive intermittent pneumatic compression (IPC) with pharmacologic thromboprophylaxis compared to pharmacologic thromboprophylaxis alone on venous thromboembolism (VTE) in critically ill adults.

**Methods/design:**

In this multicenter randomized trial, critically ill patients receiving pharmacologic thromboprophylaxis will be randomized to an IPC or a no IPC (control) group. The primary outcome is “incident” proximal lower-extremity deep vein thrombosis (DVT) within 28 days after randomization. Radiologists interpreting the lower-extremity ultrasonography will be blinded to intervention allocation, whereas the patients and treating team will be unblinded. The trial has 80% power to detect a 3% absolute risk reduction in the rate of proximal DVT from 7% to 4%.

**Discussion:**

Consistent with international guidelines, we have developed a detailed plan to guide the analysis of the PREVENT trial. This plan specifies the statistical methods for the evaluation of primary and secondary outcomes, and defines covariates for adjusted analyses a priori. Application of this statistical analysis plan to the PREVENT trial will facilitate unbiased analyses of clinical data.

**Trial registration:**

ClinicalTrials.gov, ID: NCT02040103. Registered on 3 November 2013;

Current controlled trials, ID: ISRCTN44653506. Registered on 30 October 2013.

**Electronic supplementary material:**

The online version of this article (10.1186/s13063-018-2534-6) contains supplementary material, which is available to authorized users.

## Background

Venous thromboembolism (VTE), including both deep vein thrombosis (DVT) and pulmonary embolism (PE), is a common complication of critical illness and is associated with increased morbidity and mortality [1]. Pharmacologic thromboprophylaxis is recommended for critically ill patients and is supported by high-quality evidence [2]. Despite pharmacologic thromboprophylaxis, 5 to 10% of ICU patients develop DVT [3, 4]. Data regarding the effectiveness of mechanical thromboprophylaxis including intermittent pneumatic compression (IPC) devices and graduated compression stocking (GCS) are scarce. In particular, it is unclear whether the addition of IPC to pharmacologic thromboprophylaxis provides additional protection.

The Pneumatic CompREssion for Preventing VENous Thromboembolism (PREVENT) trial is a concealed, stratified, unblinded, international, multicenter randomized controlled trial (RCT) that examines the effectiveness of adjunct IPC use with pharmacologic thromboprophylaxis compared to pharmacologic thromboprophylaxis (with unfractionated heparin (UFH) or low-molecular-weight heparin (LMWH)) alone on the incidence of proximal lower-extremity DVT in critically ill patients. The trial protocol has been published previously [5].

In this manuscript we describe the PREVENT statistical analysis plan (SAP). The SAP complies with the International Conference on Harmonization of Technical Requirements for Registration of Pharmaceuticals for Human Use, and both the “Statistical principles for clinical trials E9” and “Structure and content of clinical study reports E3” [6, 7]. This SAP identifies the procedures to be applied to the primary and secondary analyses for the entire trial cohort once trial data validation is complete. All analyses were prospectively defined as the SAP was finalized during trial implementation. The SAP was written by the principal investigator and members of the steering committee, who will remain blinded to the study results until all patients have been recruited and the database has been locked. Participant recruitment is expected to be completed by the summer of 2018. The final study report will follow the CONSORT (Consolidated Standards of Reporting Trials) 2010 guidelines for reporting randomized controlled trials [8, 9].

## Methods/design

### Study design

The PREVENT trial will enroll 2000 critically ill patients from 16 hospitals in 4 countries. The study has been approved by the Institutional Review Boards (IRBs) of the participating sites. The trial is registered at ClinicalTrials.gov: (NCT02040103) and Current Controlled Trials (ISRCTN44653506). The study is sponsored by King Abdulaziz City for Science and Technology (Grant number AT 65-34) and King Abdullah International Medical Research Center (Protocol number RC12/045/R), Riyadh, Saudi Arabia. The sponsors have no role in the study design, management or analysis.

All patients will be screened for eligibility within 48 h of ICU admission. Medical-surgical-trauma ICU patients, using accepted age cut-offs in participating adult ICUs (e.g. ≥ 14, 16 or 18 years), who weigh ≥ 45 kg, are expected to stay in ICU for ≥ 72 h and are eligible for pharmacologic thromboprophylaxis with either UFH and LMWH will be enrolled (Fig. 1). Exclusion criteria have been detailed in the protocol manuscript [5]. To enhance the generalizability of our findings, we permit the use of a broad array of IPC devices from various manufacturers intended for DVT prophylaxis. These devices include sequential devices (multi-chamber cuffs) and non-sequential devices (single-chamber cuff); the type of device will be recorded. IPC will be applied continuously for at least 18 h per day. The study intervention will continue for the duration of the ICU stay or up to 28 days after randomization; after which IPC use will be at the discretion of treating team. All enrolled patients will have a bilateral lower-extremity ultrasonography performed by a certified technologist at baseline (within 48 h of enrollment) and twice weekly thereafter until the diagnosis of a lower-extremity DVT or PE, ICU discharge, death, full mobility or 28 days (Fig. 2).

**Fig. 1 Fig1:**
[figure not shown]
Consolidated Standards of Reporting Trials (CONSORT) flow chart for the PREVENT trial

**Fig. 2 Fig2:**
[figure not shown]
Schedule of enrollment, intervention and assessment for the Pneumatic CompREssion for PreVENting Venous Thromboembolism (PREVENT) trial

### Study population

A flow chart will be constructed according to the CONSORT guidelines (Fig. 1). We will report the number of patients who were screened, met inclusion or exclusion criteria, and were eligible but not enrolled and reasons for non-enrollment. We will report the number of patients who were randomized to each group, received the allocated intervention, and had at least one ultrasonography performed.

*The Intention-to-treat population* consists of all enrolled patients and will be used for the primary analysis. All enrolled patients will be included regardless of whether or not they received the allocated intervention or had an ultrasonography performed. Post-enrollment exclusion from the intention-to-treat analysis will be restricted to withdrawal of consent to use trial data by the patient or surrogate decision-maker (SDM). However, if the patient or SDM withdraws consent for trial participation but permits collection and use of data, we will include these participants in the planned intention-to-treat analysis. Patients will also be excluded post enrollment if the eligibility criteria were not met. We plan to enroll additional patients to compensate for patients who are excluded post randomization.

*The per-protocol population* consists of all randomized patients who received the allocated intervention *and* had at least one ultrasonography performed. Although the protocol requires that a baseline ultrasonography is performed, enrolled patients may infrequently not have a single trial ultrasonography performed. For example, this circumstance may occur if a patient dies or is transferred out of the participating ICU before an ultrasonography can be performed, if the patient’s ICU stay was shorter than expected (< 72 h) or if there was to difficulty scheduling ultrasonography over weekends.

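### The intention-to-treat definition limits exclusions to withdrawn consent, then also removes randomized patients found ineligible; the two rules give different primary analysis sets

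*Protocol article*

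**What the plan says.** All the relevant rules stand in one paragraph of the protocol article, under Study population.

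- The ITT population "consists of all enrolled patients and will be used for the primary analysis".
- Neither non-receipt of the intervention nor absence of a scan removes a patient: "All enrolled patients will be included regardless of whether or not they received the allocated intervention or had an ultrasonography performed".
- One reason for removal is allowed: "Post-enrollment exclusion from the intention-to-treat analysis will be restricted to withdrawal of consent to use trial data". Patients who leave the trial but let their data be used stay in.
- A second reason follows: "Patients will also be excluded post enrollment if the eligibility criteria were not met".
- Then comes replacement: "We plan to enroll additional patients to compensate for patients who are excluded post randomization".

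On blinding, the Abstract says that radiologists reading the ultrasounds do not know the allocation, "whereas the patients and treating team will be unblinded". The Background describes the plan's authors as people "who will remain blinded to the study results until all patients have been recruited and the database has been locked". The article does not say who decides that an enrolled patient was ineligible.

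**The concern.** A rule that limits exclusions to one reason is incompatible with a sentence that adds another. Two statisticians working from this paragraph could build different primary analysis sets, and each could cite the text.

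The choice reaches far. Table 1 of the article assigns the primary, secondary and subgroup analyses to the ITT cohort, so the ambiguity touches almost every comparison.

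The second rule is also the riskier one. Randomization makes the arms comparable as randomized. Removing patients afterwards keeps that property only if the reason for removal is unrelated to arm and outcome. The paragraph sets no such condition, and the treating team knows the allocation. Enrolling replacements restores the number of patients but cannot undo a selection that differed between arms.

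**Working it through.** **1. The plan's own figure: is sample size the issue?**

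Inputs: 7% against 4% and 80% power (Abstract); 2000 patients (Study design); two-sided 5% (Statistical analysis); final level 0.048 (Interim analyses). The allocation ratio is not stated, so 1:1 is assumed.

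Per arm, n = [z(α/2)·√(2·p̄·(1−p̄)) + z(β)·√(p1(1−p1)+p2(1−p2))]² / d², with p̄ = 0.055 and d = 0.03.

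- n = [1.960·√0.10395 + 0.842·√0.1035]² / 0.0009, or 906 per arm and 1812 in total.
- With the continuity correction, (n/4)·(1+√(1+4/(n·d)))² gives 971 per arm and 1942 in total; at 0.048 the total is 1966.
- Power at 1000 per arm and the 5% level is 81.2% with the correction and 83.8% without.

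The stated 80% with 2000 patients is therefore reproduced. Losing 20 or 100 of the 2000 without replacement lowers the uncorrected power from 83.8% to 83.4% or 81.9%. Power is not the problem, and replacement does not answer the problem that remains.

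**2. The rules side by side**

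| Randomized patient | Under the restriction to consent withdrawal | Under the later sentence |
|---|---|---|
| Withdraws consent to data use | out | out |
| Stops the trial, data use allowed | in | in |
| Never treated or never scanned | in | in |
| Later found ineligible | **in** | **out, and replaced** |

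The last row cannot be reconciled. Reading the later sentence as removal from the trial, not from the ITT set, does not help: the set is still defined as everyone enrolled. The replacement sentence refers to exclusion after randomization, so the removal is not a pre-randomization screening step. None of the items under Sensitivity analyses restores the excluded patients.

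**3. How far could the risk ratio move?**

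The document gives no exclusion rate, so every input here is an assumption. Suppose no true effect and a common risk p. Let e1 and e0 be the fractions excluded from the IPC and control arms, and let excluded patients have m times the average risk. The risk left in an arm is p(1 − m·e)/(1 − e). Then p cancels:

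RR = [(1 − m·e1)/(1 − e1)] / [(1 − m·e0)/(1 − e0)]

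| e1 (IPC) | e0 (control) | m | Calculation | RR |
|---|---|---|---|---|
| 0.5% | 0 | 3 | 0.985/0.995 | 0.99 |
| 3% | 1% | 2 | (0.94/0.97)/(0.98/0.99) | 0.98 |
| 5% | 1% | 2 | (0.90/0.95)/(0.98/0.99) | 0.96 |
| 3% | 1% | 3 | (0.91/0.97)/(0.97/0.99) | 0.96 |
| 5% | 1% | 3 | (0.85/0.95)/(0.97/0.99) | 0.91 |

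At 1000 per arm the first row is 5 patients against none, and the last is 50 against 10. With m = 1, or with equal exclusion at equal risk in both arms, RR stays at 1.00. Swapping the arms reverses the direction: 3% and 1% exchanged at m = 3 gives 1/0.957 = 1.04.

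**The case against.** The other side has several good points.

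- **Exclusion of patients randomized in error can be sound.** It is defensible when ineligibility rests on facts fixed before randomization and is judged without knowledge of arm or outcome. The wording about criteria not having been met suggests entry errors and not later events. This stands, but the paragraph does not make those conditions part of the rule.
- **Procedure may be in the full protocol.** The article points to a separately published protocol, and who adjudicates eligibility could be settled there. That silence alone would be no finding. The contradiction is different: the article presents itself as the analysis plan, states the rule for the primary set, and states it two ways.
- **There are partial safeguards.** Radiologists are blinded, the plan's authors are blinded to results, and a CONSORT flow chart is promised. These limit the scope for bias but do not say which patients are in the set.

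A reader might go further in three ways that the document does not support.

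- One might infer that ineligibility will be found more often in the IPC arm because legs are inspected more there. The article says nothing of the kind. All patients are scheduled for bilateral leg ultrasound at baseline and twice weekly, and the exclusion criteria are not listed in it.
- One might infer that short stays will be relabelled as ineligible, since patients must be those who "are expected to stay in ICU for" at least 72 h. But that criterion is a forecast, which a short actual stay does not falsify, and the article treats such patients as enrolled.
- One might infer that a few removals would turn the result. For example, 70/1000 control against 50/1000 IPC events gives p = 0.060 (uncorrected chi-square), and dropping one IPC patient with DVT (49/999) gives p = 0.0478, just under 0.048. That assumes removal of exactly the patients with events in one arm, which nothing in the text implies.

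**Conclusion.** The contradiction is in the text and concerns the primary analysis set; it needs no assumption. If the ineligibility sentence is followed, the analysis omits randomized patients while keeping the ITT name, under open-label care and without a stated condition of blinded, pre-randomization judgement. That permits selection bias but does not show it.

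The size is unknown. If exclusions are only a handful, about 0.99 is the relevant illustration. The values 0.96 and 0.91 need exclusion three or five times as frequent in one arm together with tripled DVT risk among those excluded, and the document supports neither. The point is a clear error of definition to be corrected before database lock, not a prediction that the result will be biased.

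**What to change.** Delete the ineligibility exclusion from the ITT definition. Keep every randomized patient in the arm assigned, except those who withdraw consent to the use of their data. Limit the replacement sentence to those withdrawals.

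Add a sensitivity analysis without ineligible patients, in which ineligibility is judged from pre-randomization data alone, blind to arm and outcome. Report the number and reasons by arm in the flow chart.

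If the investigators prefer to keep the exclusion in the main analysis, the set should be named modified ITT, carry those same conditions, and be accompanied by an analysis of all randomized patients with usable data.

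The cost is a sentence or two. Under the preferred option a few patients enrolled in error stay in the primary analysis, which may dilute the effect slightly. Trial status reports 1620 of 2000 patients enrolled in January 2018, and the plan's authors are to stay blinded to results until lock, so the change could still be made without knowledge of the results.

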### Analysis plan

#### Baseline characteristics

We will present baseline characteristics in the two groups of the intention-to-treat cohort (Additional file 1: Online Supplement Table S1). We will compare age, sex, weight, height and Body Mass Index (BMI) between the two study groups. We will compare location immediately prior to ICU admission, Acute Physiology And Chronic Health Evaluation (APACHE) II scores, admission categories, and chronic illnesses as defined by the APACHE II system [10]. We will compare the two groups for the history of heart failure as per New York Heart Association classification and by ejection fraction (if echocardiographic assessment is performed). We will compare pre-defined pre-ICU VTE risk factors, including personal history of VTE, family history of VTE, known thrombophilic states (protein C, protein S or antithrombin deficiency, thrombotic thrombocytopenic purpura, hemolytic-uremic syndrome, activated protein C resistance, factor V Leiden thrombophilia, prothrombin gene mutation, antiphospholipid antibody, hyperhomocysteinemia), post-partum status (within 3 months), estrogen therapy (oral contraceptive or hormone replacement), active malignancy (treatment within the past 6 months or palliation), history of malignancy (within the past 5 years, other than non-melanoma skin cancer), paralysis or immobilization of a lower or upper extremity related to stroke or injury prior to this hospital admission, hospitalization in the past 3 months for any reason (excluding this hospital admission), trauma (including acute spinal cord injury, hip fracture, pelvic fracture, femoral fracture and tibial, fibular, knee or other fractures below knee), recent surgery (in the last 48 h) and acute stroke (in this index hospital admission). We will compare baseline platelet count, international normalized ratio (INR), partial thromboplastin time (PTT), creatinine and partial pressure of arterial oxygen/fraction of inspired oxygen (PaO_2_/FiO_2_) ratio. We will also compare the two study groups for mechanical ventilation, and use of vasopressors, presence of central venous catheters or dialysis catheters in the jugular, subclavian or upper extremities or in the femoral veins. We will compare the number of days from ICU admission and enrollment and use of IPC prior to randomization and duration of use.

### Intervention data

For each group we will report details regarding IPC use and the average daily duration of use (excluding study first and last days because they are usually less than 24 h, Additional file 1: Table S2). We will report reasons for not using IPCs in the IPC group and reasons for IPC use in the control group. We will classify these events as per-protocol and not per-protocol. We will classify IPC devices as sequential or non-sequential and will report the use of thigh- or knee-length sleeves and the use of foot pumps.

### Co-interventions

#### Pharmacologic thromboprophylaxis

We will compare the two study groups for the types of pharmacologic thromboprophylaxis (UFH, LMWH) at the time of enrollment. Because pharmacologic thromboprophylaxis type may be changed by the treating teams, we will report the percentage of patients who received each type of pharmacologic thromboprophylaxis (UFH, LMWH) at any time during the intervention period and for > 50% of the study period.

#### Therapeutic anticoagulation, antiplatelet therapy and anticoagulation for continuous renal replacement therapy

We will compare the two study groups with regard to the number of patients who receive therapeutic anticoagulation (with any agent) for reasons other than VTE during the study period, and the duration of therapeutic anticoagulation. We will report the anticoagulation use for continuous renal replacement therapy (CRRT) (citrate or heparin) during the study period. We will document the use of other anticoagulants during the intervention period (warfarin, other orally administered anticoagulants, danaparoid, argatroban, fondaparinux, lepirudin, others). We will also compare the use of thrombolytic therapy (tissue plasminogen activator (tPA), streptokinase, urokinase) and the use of antiplatelet agents (including aspirin, clopidogrel, ticlopidine, glycoprotein IIb/IIIa inhibitor).

#### Graduated compression stockings

The use of graduated compression stockings (GCS) is not permitted in the trial. If used, we will document the duration and the reasons for use. We will report the number of patients who used GCS in each group and the duration of their use.

#### Central venous catheters, dialysis and arterial catheters

Between groups, we will compare the presence and number of days in situ of central venous catheters or dialysis catheters in the femoral, internal jugular, and subclavian veins, as well as, the presence of a peripherally inserted central catheter (PICC) in the upper extremities. We will also document the presence of arterial lines in the femoral or dorsalis pedis arteries.

#### Other co-interventions

Between groups, we will compare any use of mechanical ventilation, vasopressors, CRRT, intermittent dialysis, or peritoneal dialysis during the intervention period. We will also compare transfusions of packed red blood cells, fresh frozen plasma, platelets and cryoprecipitate between groups. Finally, we will compare the administration of statins, factor VII and vitamin K between treatment groups.

#### Mobility

Because mobility may influence the risk of DVT and because IPC may interfere with mobility, we will compare the highest level of mobility achieved each day and during the intervention duration between treatment groups. Mobility level will be assessed using a pre-defined continuous scale (0 nothing; 1 transfer from bed to chair without standing, 3 sitting in bed/exercises in bed, 4 sitting at edge of bed, 5 standing, 6 transfer from bed to chair with standing, 7 marching in place, 8 walking, and unknown) [11].

#### Diagnostic testing

As this is an open-label study, we will compare the number of diagnostic tests performed for VTE detection between study groups to assess for potential ascertainment bias. Specifically, we will compare the study groups for the number of patients who had undergone at least one ultrasonography of the lower extremities, the time to the first ultrasonography and the number of ultrasonographs of the lower extremities per patient. We will also compare the two groups for the number of patients who underwent ultrasonography of the upper extremities and neck to evaluate for thrombosis, computerized tomography (CT) scan of the chest to evaluate for PE, lung ventilation-perfusion scans, transthoracic and transesophageal echocardiograms (for all indications) and CT scan of the abdomen to evaluate for thrombosis.

### Primary outcome

The primary outcome is incident proximal lower-extremity DVT detected after the third calendar day of enrollment during the intervention period (defined as the number of calendar days from enrollment until the end of the intervention period; that is, diagnosis of lower-extremity DVT, PE, ICU discharge, death, full mobility or 28 days). The primary outcome tests the primary hypothesis that IPC reduces incident proximal lower-extremity DVT (Additional file 1: Table S3).

